## Abstract

**Background:**

Anxiety and depressive disorders are highly prevalent, common mental disorders globally, but access to efficacious, high-reach treatment remains scarce. Although digital cognitive-behavioral therapies (CBTs) demonstrate efficacy and scalability, they remain limited in enhancing positive affect (PA) and reward processing, which are core deficits underlying anhedonia, a key transdiagnostic symptom. This randomized controlled trial (RCT) evaluates a locally tailored, guidance-on-demand, low-intensity Digital Positive Affect Intervention (PAI) developed to improve positive valence systems while alleviating symptoms in adults and university students in Singapore.

**Methods:**

This single-blind, two-arm, pragmatic RCT will recruit 1,200 community-dwelling adults with mild-to-moderate symptoms of anxiety or depression. Participants will be randomly assigned in a 1:1 allocation to either the Digital PAI or the Self-Monitoring Placebo as the placebo control across six weeks. Digital PAI comprises six weekly 30-minute self-guided online sessions coupled with thrice-daily ecological momentary interventions (EMIs) focusing on PA regulation. The Self-Monitoring Placebo offers non-therapeutic mood-tracking instructions three times daily. The same ecological momentary assessments (EMAs) are administered in both groups after each EMI prompt. Clinical outcome assessments are administered at baseline, mid-treatment (Week 3), post-treatment (Week 6), and 3-month, 6-month, and 12-month follow-ups. Primary outcomes are changes in anxiety and depression severity (Generalized Anxiety Disorder-7 [GAD-7] and Patient Health Questionnaire-9 [PHQ-9]). Secondary outcomes comprise anhedonia, emotion regulation, reward processing, and sleep quality. Randomly selected subsamples will provide wearable data. Analyses will harness multilevel modeling, generalized estimating equations, causal mediation, structural equation modeling, and precision medicine methods to evaluate treatment efficacy, change mechanisms, and moderators.

**Discussion:**

This RCT examines the proximal (immediate) and distal (long-term) efficacy of a locally tailored PAI, aligned with cultural values and context, that combine PA improvement strategies with scalable digital delivery to integrate skills into daily routines and settings. It fills essential knowledge gaps in digital mental health research by addressing the positive valence system and incorporating prospective EMA and wearable assessments in real-time. If successful, the Digital PAI may inform stepped-care and stratified care models as well as AI-triaging approaches. These efforts may contribute to more extensive implementation of data-driven, patient-centered care in culturally diverse, resource-limited contexts.

**Trial registration::**

ClinicalTrials.gov ID (NCT06978257)

**Date of trial registration::**

April 15, 2025

**URL of trial registration::**

https://clinicaltrials.gov/study/NCT06978257.

**Supplementary information:**

The online version contains supplementary material available at 10.1186/s12888-025-07372-4.

## Background

Anxiety and depressive disorders are common mental disorders worldwide. Epidemiological meta-analyses indicated that 12-month prevalence rates ranged from 2.4 to 29.8% for anxiety disorders [1–3] and from 1.6 to 8.0% for depressive disorders [4–6]. These conditions are closely linked to disruptions in psychosocial functioning, affecting academic performance, work, and personal relationships [7–9]. Neurocognition [10, 11], physical health [12, 13], and quality of life (QOL) [14] could also be severely compromised by untreated anxiety and depressive disorders. At the societal level, the economic costs of these common mental disorders can amount to between 20.5 and 333.7 billion USD [15, 16]. Despite this reality, notable treatment gaps exist, with between 51.7 and 83.2% of those meeting the criteria for anxiety or depressive disorders not receiving adequate mental health support [17, 18]. These treatment gaps highlight the importance of testing cost-effective, empirically supported digital mental health interventions (DMHIs) that can improve early detection, increase outreach, and enhance access to diverse populations with anxiety and depressive disorders.

DMHIs have primarily adopted cognitive-behavioral therapy (CBT) orientations through apps, computers, tablets, and other digital platforms, given their well-documented comparative efficacy for anxiety and depressive disorders. Theoretically, digital CBT options address maladaptive avoidant behaviors, negative self-talk patterns, and related action and thought repertoires via a plethora of psychoeducational and emotion regulation (ER) skills [19]. Digital CBT lessons can be designed as fully self-guided interventions or coupled with low-intensity, user-initiated guidance-on-demand; medium-intensity, asynchronous, text-based coaching; or high-intensity, synchronous telehealth psychotherapy [20]. The benefits of low-intensity, guided, digital CBT include its scalability, which requires minimal human resources for coaching while enhancing accountability through interactive practices, progress monitoring, constructive feedback, and reinforcement [21]. To this end, such changes in repertoires of action and thought patterns are intended to be extended to daily, real-world, naturalistic settings, which may ultimately lead to symptom relief and related improvements.

Mounting meta-analytic data highlights the short- and long-term comparative efficacy of digital CBTs to remedy anxiety and depressive symptoms [22–26]. In the short term, digital CBTs have reliably generated moderate to large differential effect sizes across randomized controlled trials (RCTs). For instance, digital CBTs yielded large effect sizes in targeting anxiety disorders (Hedge’s *g* = 0.80), with notable improvements for generalized anxiety disorder (GAD), panic disorder, and social anxiety disorder (SAD), even with fully self-guided formats [22]. Moreover, guided digital CBTs have demonstrated clinically meaningful efficacy in alleviating depression and insomnia symptoms, with comparable outcomes to face-to-face modalities [23, 25, 26]. Similarly, even self-guided digital CBT for insomnia, which frequently co-occurs with anxiety and depressive disorders, generated small-to-moderate efficacy in reducing anxiety (Cohen’s *d* = −0.29) and depression symptoms (*d* = −0.42) [23]. Notably, the benefits of guided and fully self-guided digital CBTs were sustained across 12 months or more after randomization [24]. Guided digital CBTs produced stronger long-term decreases in anxiety and depression symptoms relative to controls (*g* = −1.86 to −0.31). Fully self-guided digital CBTs also yielded enduring comparative gains (*g* = −0.51 to −0.09). Collectively, digital CBTs may facilitate clinically meaningful mental health improvements for anxiety and depressive disorders in scalable ways.

Although standard digital CBT provides evidence-based, scalable ways to remedy anxiety and depression symptoms, its ability to offer targeted enhancements in positive affect (PA) and alleviate anhedonia (i.e., deficits in motivation or pleasure) remains limited. Standard digital CBTs typically focus on reducing avoidant patterns, maladaptive thinking, and negative emotions, utilizing behavioral activation [27], cognitive restructuring [28], and exposure therapy [29]. Inadequate focus is directed towards fostering approach-driven action repertoires, gratitude [30, 31], savoring [32, 33], and reward sensitivity practices [34, 35], which have been shown to cultivate positive mood states [36]. This shortcoming of digital CBTs is noteworthy since blunted PA, increased anhedonia, and reward insensitivity are prominent in both anxiety and depressive disorders [37] and predict long-term trajectories [38]. Moreover, cultivating PA can enhance resilience, foster lasting recovery, and mitigate acute anxiety and depression symptoms [39, 40]. PA has been consistently linked to broadened cognitive attention, enhanced attentional flexibility, extended attention spans, heightened awareness of positive stimuli, improved learning, and the opening of new avenues of action [41, 42]. However, PA has received less attention in clinical psychological science and DMHIs than negative emotions. Taken together, evaluating non-standard digital CBT types that are designed to address suboptimal reward processing, especially digitally delivered adaptations of Positive Affect Treatment (PAT) [39], is an essential logical next step. A locally tailored, scalable, digitally delivered Positive Affect Intervention (PAI), informed by the face-to-face delivered PAT, may confer measurable gains beyond symptom reduction by enhancing the ability to create and maintain pleasurable activities and feelings in meaningful engagements. Digital PAI may impact both symptom reduction and PA improvement by boosting meaningful activities, reward sensitivity, and social engagements through components such as positive event scheduling, self-compassion training, and savoring [43]. Rigorous, well-implemented RCTs are, therefore, necessary to test whether Digital PAI can pragmatically improve positive valence systems in diverse clinical samples.

### Study aims and hypotheses

Given the theories and logic outlined, this RCT implements a two-arm RCT that aims to evaluate the efficacy of a low-intensity, guidance-on-demand, 6-week Digital PAI vs. a Self-Monitoring Placebo control for adults with mild-to-moderate anxiety or depression. This Digital PAI was adapted from the 15-week face-to-face PAT [44], as detailed in the Method. It aims to equip individuals with diverse evidence-based ER skills that may enhance positive mood states and reduce anhedonia, including goal setting, gratitude, personal strengths, positive reappraisal, savoring, and exercises linked to reward sensitivity.

This RCT is unique in several ways. First, it examines how the Digital PAI might improve sleep outcomes. This inquiry is essential, given the high rates of sleep disturbances in anxiety and depressive disorders [45, 46]. Moreover, deficits in PA and reward sensitivity in anxiety and depression have been intimately linked to sleep disturbances [47, 48], which the Digital PAI may remedy. Second, the 12-month time horizon is relatively uncommon in DMHI trials [24], which facilitates the evaluation of long-term promises and pitfalls. Third, evaluating the efficacy of the Digital PAI in Singapore may advance implementation science across various cultures, thereby maximizing impact and scalability.

Our a priori hypotheses were twofold. First, we predicted that the Digital PAI would yield significantly greater improvements in anxiety and depression outcomes than the Self-Monitoring Placebo. Clinical outcomes were defined in binary terms, including remission indexed by Generalized Anxiety Disorder-7 (GAD-7) [49] and Patient Health Questionnaire (PHQ-9) [50] scores ≤ 4 as well as clinically significant improvement [51]. Clinical outcomes were also operationalized dimensionally, as scores from baseline to 6-week, 3-month, 6-month, and 12-month follow-ups. Second, we hypothesized that the Digital PAI would generate significantly more improvements in various secondary outcomes indexed dimensionally: anhedonia, attentional control, ER, generalized anxiety disorder (GAD) severity, negative affect (NA), panic disorder symptoms, perceived stress, PA, positive valence systems, self-compassion, sleep quality, and thinking errors.

The remaining aims were exploratory. We aim to examine theory-driven *mediators* (variables that account for why and how the app works) [52] and *moderators* (or effect modifiers; variables that pinpoint for whom the app works) [53]. Diverse theory-driven neurocognitive and psychosocial variables are collected, as detailed in the next section, while maintaining an exploratory approach due to the limited existing studies on this topic.

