PHQ-9	X		X	X	X	X	X
ACS		X	X	X	X	X	X
ATQ		X	X	X	X	X	X
DARS		X	X	X	X	X	X
ERQ		X	X	X	X	X	X
MHC-SF		X	X	X	X	X	X
PANAS		X	X	X	X	X	X
PSQI		X	X	X	X	X	X
PSS		X	X	X	X	X	X
PVSS		X	X	X	X	X	X
SCS-SF		X	X	X	X	X	X
2BT		X					
BLERT		X					
Brief COPE		X					
CDS		X					
CTQ		X					
GADQ-IV		X					
GNG		X					
IRI		X					
PDSR		X					
Personality		X					
PHI		X					
PSAS		X					
RSES		X					
SCI		X					
SHPS		X					
Loneliness		X					
WCST		X					
CRQ				X			
STQ				X			
HAT			After each session				

‘X’ marks the time point of measurement administration

*2BT* 2-Back Task, *ACS* Attentional Control Scale, *ASRM* Altman Self-Rated Mania, *ATQ* Automatic Thoughts Questionnaire, *BLERT* Bell Lysaker Emotion Recognition Test, *Brief COPE* Brief Coping Orientation to Problems Experienced, *CDS* Cognitive Distortions Scale, *CRQ* Cultural Relevance Questionnaire, *CTQ* Childhood Trauma Questionnaire, *DARS* Dimensional Anhedonia Rating Scale, *ERQ* Emotion Regulation Questionnaire, *GAD-7* Generalized Anxiety Disorder-7, *GADQ-IV* Generalized Anxiety Disorder Questionnaire-Fourth Edition, *GNG* Go/No-Go, *HAT* Helpful and Hindering Aspects of Therapy, *IRI* Interpersonal Reactivity Index, *MHC-SF* Mental Health Continuum Short Form, *PANAS* Positive and Negative Affect Schedule, *PDSR* Panic Disorder Self-Report, *PHI* Pemberton Happiness Index, *PHQ-9* Patient Health Questionnaire-9, *PSAS* Pre-Sleep Arousal Scale, *PSQI* Pittsburgh Sleep Quality Index, *PSS* Perceived Stress Scale, *PVSS* Positive Valence Systems Scale, *RSES* Rosenberg Self-Esteem Scale, *SCS-SF* Self-Compassion Scale-Short Form, *SCI* Sleep Condition Indicator, *SHPS* Sleep Hygiene Practice Scale, *STQ* Satisfaction with Treatment Questionnaire, *WCST* Wisconsin Card Sorting Test

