### Symptom assessments

Symptom severity will be assessed using a range of psychometrically reliable and valid self-report measures administered at various time points to evaluate both the proximal and distal differential efficacy of Digital PAI. The GAD-7 [49], PHQ-9 [62], and Dimensional Anhedonia Rating Scale (DARS) [63] are administered at screening or baseline, mid-treatment (Week 3), post-treatment (Week 6), as well as 3-, 6-, and 12-month follow-ups to monitor changes in anxiety, depressive, and anhedonia symptoms, respectively. The ASRM [59] is administered at the screening stage to assess possible exclusionary symptoms of mania. Furthermore, the symptoms of GAD and panic disorder are assessed using the GAD Questionnaire-Fourth Edition (GADQ-IV) [64] and the Panic Disorder Self-Report (PDSR) [65], respectively, at baseline, and these measures align with the Diagnostic and Statistical Manual, Fifth Edition (DSM-5) criteria [66]. This staggered yet holistic measurement method allows the assessment of both proximal symptom change and sustained maintenance of gains. Refer to Appendix B for more details on the psychometric properties of each assessment.

Additionally, participants may discontinue the Digital PAI or Self-Monitoring Placebo as they wish at any time. Study staff may stop participation if safety concerns arise, including the detection of suicidality at any follow-up assessment. In those scenarios, a suicide risk assessment and brief safety planning will be conducted for these participants.

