### Process-based assessments

Most process-based assessments are administered at baseline to determine individual differences in psychosocial factors that may moderate or predict treatment response and distal outcomes. These assessments consist of the Childhood Trauma Questionnaire (CTQ) [67] to capture retrospective childhood maltreatment encounters; the Brief Coping Orientation to Problems Experienced (Brief COPE) [68] to measure coping strategies; the performance-based Bell Lysaker Emotion Recognition Test (BLERT) [69] to measure socioemotional processing; and the Emotion Regulation Questionnaire (ERQ) [70] to capture cognitive and behavioral ER habits. Further, baseline assessments measure global well-being with the Pemberton Happiness Index (PHI) [71]; perceived loneliness with the University of California, Los Angeles (UCLA) Loneliness measure [72]; subjective appraisal of stress with the Perceived Stress Scale (PSS) [73]; and personality traits with the Revised NEO Personality Inventory (NEO-PI-R) self-report [74]. In addition, at baseline, this RCT measures levels of PA and NA from the Positive and Negative Affect Schedule (PANAS) [75]; reward processing with the Positive Valence Systems Scale (PVSS) [76]; psychosocial well-being with the Mental Health Continuum Short Form (MHC-SF) [77]; trait self-compassion with the Self-Compassion Scale-Short Form (SCS-SF) [78, 79]; and self-esteem with the Rosenberg Self-Esteem Scale (RSES) [80]. Thinking errors are measured with the Cognitive Distortions Scale (CDS) [81] and Automatic Thoughts Questionnaire (ATQ) [82]. Trait empathy is assessed using the Interpersonal Reactivity Index (IRI) [83], a self-report measure. Most of these self-reports and 1 performance-based assessment (BLERT) will be collected only at baseline. However, a specific subset (ACS, ATQ, DARS, ERQ, GAD-7, MHC-SF, PANAS, PHQ-9, PSQI, PSS, PVSS, and SCS-SF) will be re-administered at mid-treatment, post-treatment, as well as 3-, 6-, and 12-month follow-ups to assess change across time (Table 1 and Appendix B).

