### Sleep assessments

Sleep functioning and quality are assessed using four self-report assessments administered at baseline, mid-treatment, post-treatment, as well as at 3-, 6-, and 12-month follow-ups to evaluate both proximal and distal changes in sleep patterns. The Sleep Condition Indicator (SCI) [89] assesses insomnia symptoms in ways consistent with DSM-5 diagnostic criteria [66]. The Pre-Sleep Arousal Scale (PSAS) [90] assesses cognitive and somatic arousal during the pre-sleep period, providing insights into factors that may interfere with more rapid sleep onset. The Sleep Hygiene Practice Scale (SHPS) [91] measures actions that help or hinder healthy sleep rhythms and routines. Finally, the Pittsburgh Sleep Quality Index (PSQI) [92] measures global sleep quality across several domains, including daytime dysfunction, sleep duration, disturbances, and sleep onset latency. Together, these self-reports offer a multidimensional assessment of sleep-focused processes that may interact with or predict treatment response (Table 1 and Appendix B).

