#### Mediation analysis

To evaluate plausible mechanisms of change in treatment [126], both causal mediation analysis [127, 128] and structural equation modeling (SEM) [129, 130] will be conducted. Causal mediation analysis will be performed using the *mediation* package [131] to compute average causal mediation effects (ACME) and average direct effects (ADE), facilitating inferences about temporally sequenced mediators such as ER and social cognition factors. Simultaneously, SEM will be harnessed using the *lavaan* package to assess multiple mediators while accounting for the nested, longitudinal data structure and measurement error [129]. Latent variable analysis, including core psychological concepts (e.g., anhedonia, personality) using confirmatory factor analysis (CFA) with FIML estimation and other missing data management strategies described above, will be conducted. These complementary methods provide both causal inferences under plausible outcome frameworks and parameter estimates of indirect effects, enabling a stringent and theory-driven understanding of how the Digital PAI operates.

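### Panic symptoms and GAD severity are hypothesised to improve, but their scales are scheduled at baseline only; the sleep schedule and the social-cognition mediator also conflict with the measurement plan

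*Protocol article*

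**What the plan says.** **Hypothesis.** Study aims and hypotheses predicts that Digital PAI will outperform the control on 12 secondary outcomes measured dimensionally. The list includes "generalized anxiety disorder (GAD) severity, negative affect (NA), panic disorder symptoms".

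**Instruments for GAD and panic.** Symptom assessments assigns these to "the GAD Questionnaire-Fourth Edition (GADQ-IV) [64] and the Panic Disorder Self-Report (PDSR) [65], respectively, at baseline". In Table 1, where an X "marks the time point of measurement administration", each has one X, under Baseline.

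**Repeated measures.** Process-based assessments states that "a specific subset (ACS, ATQ, DARS, ERQ, GAD-7, MHC-SF, PANAS, PHQ-9, PSQI, PSS, PVSS, and SCS-SF) will be re-administered at mid-treatment" and at the later visits. The GADQ-IV and PDSR are not among the 12.

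**Sleep.** Sleep assessments states: "Sleep functioning and quality are assessed using four self-report assessments administered at baseline, mid-treatment, post-treatment, as well as at 3-, 6-, and 12-month follow-ups". The four are SCI, PSAS, SHPS and PSQI, and the stated purpose is to evaluate change. In Table 1 only the PSQI is repeated.

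**Mediation.** Mediation analysis describes its method as "facilitating inferences about temporally sequenced mediators such as ER and social cognition factors". Process-based assessments says the BLERT is taken at baseline only, and Table 1 shows the same for the IRI.

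**Attentional control.** Neurocognition assessments says its measures, the ACS included, are given at baseline alone. Table 1 and the list of 12 repeat the ACS at every visit.

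**Analysis.** The section on primary and secondary outcomes models all outcomes over baseline, Week 3, Week 6 and Months 3, 6 and 12, with a group-by-time interaction.

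**The concern.** A hypothesis of greater improvement needs at least one measurement after randomisation. If a named outcome has none, it cannot be analysed as planned. At reporting it would have to be dropped or replaced by another scale, and a reader could not tell whether that choice was made before or after the data were seen.

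The same logic applies to mediators: a variable fixed before allocation cannot carry an effect of allocation.

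Timing matters because Trial status says enrolment and data collection are under way. If Table 1 is the schedule in use, every participant who passes Week 6 without these scales is a value that cannot be recovered.

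**Working it through.** The protocol gives no figure to reproduce here. The check maps each promised outcome or mediator to its instrument and counts its scheduled assessments after baseline.

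**1. The 12 secondary outcomes against Table 1.** There are five possible post-baseline visits: Week 3, Week 6, Months 3, 6 and 12.

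| Outcome in the hypothesis | Instrument | Post-baseline assessments |
|---|---|---|
| Anhedonia | DARS | 5 |
| Attentional control | ACS | 5 |
| Emotion regulation | ERQ | 5 |
| GAD severity | GADQ-IV | 0 |
| Negative affect | PANAS | 5 |
| Panic symptoms | PDSR | 0 |
| Perceived stress | PSS | 5 |
| Positive affect | PANAS | 5 |
| Positive valence systems | PVSS | 5 |
| Self-compassion | SCS-SF | 5 |
| Sleep quality | PSQI | 5 |
| Thinking errors | ATQ (CDS at baseline only) | 5 |

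So 12 − 2 = 10 outcomes have a repeated instrument.

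**2. Is this a slip in the table?** The measures repeated in Table 1 are GAD-7, PHQ-9, ACS, ATQ, DARS, ERQ, MHC-SF, PANAS, PSQI, PSS, PVSS and SCS-SF. These are the same 12 as in Process-based assessments. For the GADQ-IV and PDSR, Symptom assessments also says baseline. Three places agree with each other and conflict with the hypothesis.

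**3. Can the planned model be fitted?** With one time point per person, time does not vary, so the group-by-time coefficient is not identified. The only available contrast is the group difference at baseline, which randomisation makes zero in expectation.

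**4. Does another scheduled measure fill the gap?**
- Panic: no other panic scale is scheduled, and none of the ten momentary states in the brief EMAs is panic.
- GAD severity: the GAD-7 has five post-baseline assessments, but it is already a primary outcome.

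**5. Sleep.** The Sleep assessments text implies 4 scales × 5 visits = 20 post-baseline administrations per participant. Table 1 gives 1 × 5 = 5. The difference of 15 is SCI, PSAS and SHPS at five visits each. The section's opening sentence gives change as the purpose, while its closing sentence describes prediction of response and points to Table 1.

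**6. Social cognition.** Under Study design, participants are randomised at the end of the baseline assessment. Let M(1) and M(0) be the mediator under treatment and control, and Y the outcome. The average causal mediation effect is E[Y(t, M(1)) − Y(t, M(0))]. For a pre-randomisation score M(1) = M(0), so the effect is zero by construction. Any non-zero estimate would reflect chance imbalance at baseline. Emotion regulation, named beside it, is measured by the ERQ and has five post-baseline assessments.

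**The case against.** **The hypothesis names a construct, not the GADQ-IV, and the GAD-7 is repeated.** This stands in part: related follow-up data on GAD severity will exist. But the protocol lists GAD severity separately from the primary anxiety outcome and pairs GAD symptoms with the GADQ-IV. Using the GAD-7 would count the primary outcome twice. The argument does not reach panic symptoms.

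**Sleep.** A reader might infer that most of the sleep aim has no data. The documents do not support that. They contradict each other, and nothing shown says which schedule is being run. The hypothesised outcome is sleep quality, which the PSQI measures at all visits. Only if Table 1 governs is change in insomnia symptoms, pre-sleep arousal and sleep hygiene lost. Sleep actigraphy would not replace it, since it covers a random subsample sharing 25 devices and only the six intervention weeks.

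**Mediation is exploratory, and social cognition is one example.** This stands as to weight. The Discussion gives anhedonia, attentional control and reward sensitivity as example mechanisms, and all three are repeated (DARS, ACS, PVSS). Classing the IRI, described as trait empathy, under social cognition is also a matter of interpretation. The named mediator class is still untestable with either scale.

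**The ACS sentence threatens no aim.** Agreed: follow-up data are planned, and only the wording is wrong.

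**Fig. 1 and Appendix B are not shown.** True. They might reveal the intended schedule, but they cannot make the visible text agree with itself. Nor is this the condensation usual in an article, because a full schedule and an explicit list of repeated measures are printed.

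**Conclusion.** The point holds in this form:

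- **Panic symptoms:** no follow-up data on any reading of the text shown. One of 12 secondary outcomes cannot be tested.
- **GAD severity:** no follow-up data on its assigned instrument, and only the primary GAD-7 as a related measure. This is a second outcome of the 12 without separate data.
- **Sleep:** a contradiction to be resolved, not a demonstrated loss. Sleep quality is testable with the PSQI on either schedule.
- **Social cognition:** cannot be a mediator as measured. The effect is confined to an exploratory aim.
- **ACS:** a wording error only.

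Both primary outcomes, and all four secondary outcomes named in the abstract, have repeated instruments. It would be wrong to infer that the trial's main aims are compromised. The conclusion on panic and GAD assumes that Table 1 and the text agreeing with it describe what is being collected.

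**What to change.** Establish which schedule is in use, choose one of two routes, and make the text and Table 1 agree.

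**Route A, measure them.** Add the PDSR and GADQ-IV at least at Week 6 and Months 3, 6 and 12: 2 × 4 = 8 extra questionnaires per participant. If the Sleep assessments text is what was intended, SCI, PSAS and SHPS at all five visits add 3 × 5 = 15, or 23 in total. Completion times are not given, so the burden cannot be sized from the document. It should be weighed against the 50% attrition already assumed. Recruitment began on 1 April 2025, so participants already past those visits will lack the added scales. That gap is set by calendar date and not by arm, so these outcomes can be compared between arms among participants who reach each visit after the change, and this should be stated in advance.

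**Route B, drop them.** Remove panic symptoms and GAD severity from the second hypothesis. Correct Sleep assessments so that the PSQI is the only sleep scale analysed for change, and describe GADQ-IV, PDSR, SCI, PSAS and SHPS as baseline predictors or moderators. This costs wording only.

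**Under either route,** remove social cognition from the mediators and keep BLERT and IRI as moderators or predictors, the role Process-based assessments already gives to its baseline measures. In Neurocognition assessments, exempt the ACS from the baseline-only statement. The registry entry should be checked for the same outcomes.
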